#### Primary outcomes

2.5.1

1.The total effective rate of PUD treatment will be calculated as (clinical cure + markedly effective + effective)/total number of participants. Efficacy will be assessed by Sakita–Miwa's method.^[22]^ First, ulcer healing status will be classified into 6 categories:A1: the ulcer is round or elliptical, with a thick and white covering in the center; it can be accompanied by errhysis or blood clots and surrounded by obvious swelling, hyperemia, and oedema.A2: the ulcer is covered by yellow or white patches, with no bleeding and less swelling and edema.H1: the ulcer is healing; the coating of the ulcer becomes thin and subsides, hyperemia and edema disappear around the ulcer, and new capillaries appear.H2: the ulcer becomes shallow and small; the surrounding mucosa plica is central to the ulcer.S1: the white coating of the ulcer disappears, and the new ulcer mucosa is red.S2: the new ulcer mucosa changes from red to white.Then, the efficacy will be ranked according to the following 4 levels based on ulcer rehabilitation and recovery:Clinical cure: the ulcer completely heals with or without a scar.Markedly effective: the ulcer heals to grade H2 or improves 2 grades.Effective: the ulcer heals to grade H1 or improves by 1 grade.Noneffective: no efficacy by endoscopic observation.2.The quality of ulcer healing will be classified as follows by histopathological examination using Pan's criteria^[23]^:Good: integral villus and epithelium, many glands, good morphology, many capillaries, and limited inflammatory cell infiltration.Fair: short villus, incomplete or rough epithelium, fewer glands, structural distortion, few capillaries, and moderate inflammatory cell infiltration.Poor: few new epithelial cells, poor epithelium integrity, poor morphology of villus and glands, very few capillaries, and a large number of inflammatory cells.3.The changes in SQD symptoms will be assessed based on the Spleen Qi Deficiency Symptoms Grading and Quantifying Scale (SQD scale) score.^[19]^ This is a modified version of the classic scale that has a total of 15 items to assess 7 main symptoms and 8 secondary symptoms. Four aspects of SQD symptoms will be assessed, including severity, duration per episode, number of attacks per day, and number of affected days per week. The total score of each item is the sum of points for the 4 aspects in all items (items assessing the main symptoms receive double weight). The score ranges from 0 to 283 points, and a higher score indicates worse symptoms (see details in Supplementary file).

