### Study visits

2.6

We will visit patients at baseline and at weeks 6, 12, 26, 52, and 104. In addition to the baseline measures of the outcomes, patients will undergo an eligibility assessment and provide demographic data, including gender, age, marital status, living situation, complications, medication history, and allergy history at baseline. During follow-up, we will examine ulcer histopathology at weeks 12 and 26; perform physical examinations, laboratory tests, and an electrocardiogram at weeks 12, 26, and 52; and examine *H pylori* infection and gastric function and perform gastroscopy at weeks 12, 26, 52, and 104. SQD symptoms, AEs, and concomitant treatments will be assessed or recorded at all follow-up visits. Table 2 gives an overview of the trial visits.

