### Sample size estimation

2.9

The main objective of this trial is to assess the effects of HGMX compared with placebo on the total effective rate. Therefore, the sample size estimation is based on the formula for a superiority design.^[24]^ Because there are no previous studies available for reference, we estimated a *P* of .85 (total effective rate in the two groups receiving HGMX) and a *P*_0_ of .65 (total effective rate in the 2 groups receiving placebo) according to the results of our pilot survey and expert opinions. In addition, we adopted a type I error (α) of 0.05, a type II error (β) of 0.2, and a maximum drop-out rate of 15%. Based on these assumptions and our funding constraints, we computed a sample size of 360, with 90 in each group.

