### Data analysis

2.10

The primary outcome data will be analyzed using the intention-to-treat population, in which all patients will be maintained in their initial group assignment regardless of compliance and contamination, and missing data will be imputed using the last observation carried forward method. Meanwhile, we will also conduct a sensitivity analysis with the per-protocol population. The safety outcomes will be analyzed using a safety population including all participants who received treatment at least once. Mid-term and final data analyses will be performed at the end of week 52 and 104, respectively.

Normality will be detected using the Kolmogorov-Smirnov method. Normal continuous variables will be described using the mean and standard deviation and compared using a *t* test or analysis of variance. Non-normal continuous variables will be described using the median and interquartile range and analyzed with the Mann–Whitney *U* test. Categorical variables will be presented as the frequency and percentage and compared using Pearson *χ*^2^ test. The boundary of significance for the *P* value will be .05, which will be adjusted using the O’Brien & Fleming method for multiple comparisons.

According to our factorial design, we will explore whether there exists an interaction between HGMX and rabeprazole. If there are no significant interaction effects, we will compare the main effects of HGMX and rabeprazole. In addition, we will perform subgroup analysis stratified by type of PUD (GU vs. DU) and *H pylori* infection status (yes vs no). All statistical analyses will be conducted in Stata v14.0 software.

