### Trial monitoring

2.11

An independent data monitoring committee (DMC) will be found, which will be responsible to supervise the overall efficacy and safety of the trial. The DMC will have right to decide an interim data analysis and to stop the trial if obvious benefits or harms are observed.

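### O'Brien-Fleming is named as the correction for multiple comparisons, but it does not control error across the three unranked primary outcomes

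*Protocol article*

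**What the plan says.** All references are to the protocol article.

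- **Section 2.10, Data analysis.** The threshold is 0.05, "which will be adjusted using the O’Brien & Fleming method for multiple comparisons". The same section fixes two analysis times: "Mid-term and final data analyses will be performed at the end of week 52 and 104, respectively". It gives no boundary values or information fraction.
- **Section 2.5.1, Primary outcomes.** Three are listed, with no order, no co-primary rule and no primary visit: the total effective rate, the histological quality of ulcer healing ("The quality of ulcer healing will be classified as follows by histopathological examination"), and the change in SQD score.
- **Section 2.6, Study visits.** The rate is available four times ("perform gastroscopy at weeks 12, 26, 52, and 104"), histology at weeks 12 and 26 only, and the SQD score at all five follow-up visits.
- **Section 2.9, Sample size estimation.** "The main objective of this trial is to assess the effects of HGMX compared with placebo on the total effective rate". Section 2.10 does not carry this priority into the confirmatory analysis.
- **Section 2.4.4, Extension period.** Weeks 53 to 104 are observational, with all interventions stopped.

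**The concern.** This is a stated rule, not a detail left to an analysis plan, and the named method does not do the stated job. An O'Brien-Fleming boundary divides the type I error of one hypothesis over successive looks at growing data. It does nothing for the choice among several outcomes.

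The sentence has two possible meanings, and neither works. If it refers to the outcomes, the method is the wrong one. If it refers to the week-52 and week-104 analyses, the three primary outcomes have no stated correction. Either way, success on any one of three unranked outcomes could be presented as confirmatory, with a false-positive risk well above the 5% that the sample size assumes.

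The fit to the two analyses is also poor. On the natural reading, all histology is in hand by the mid-term analysis, so the final analysis adds none. For the rate and the SQD score, week 104 measures a patient one year after treatment stopped. That is a different time point, not the remaining information on the week-52 effect.

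**Working it through.** **1. The plan's own figure.** Section 2.9 gives rates of 0.85 and 0.65, alpha 0.05, beta 0.2, 15% drop-out and a total of 360 (90 in each of four groups). With the simple pooled formula, two-sided:

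n = 2 × 0.75 × 0.25 × (1.960 + 0.842)² / 0.20² = 73.6, so 74; 74 / 0.85 = 87.1, so 88; 88 × 4 = 352.

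This is close to 360. It is reached with the unadjusted 0.05 and with the two-group n given to each of the four groups. No allowance for multiplicity is visible.

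**2. Boundary levels.** For two looks at overall two-sided 0.05, the levels depend on the information fraction, which must be assumed:

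| Assumed fraction | Week 52 | Week 104 |
|---|---|---|
| 0.5 | p < 0.0052 (z 2.797) | p < 0.0480 (z 1.977) |
| 0.75 | p < 0.020 | p < 0.044 |

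**3. What the boundary does for one outcome.** With levels 0.0052 and 0.048, simulated type I error for a single outcome over the two weeks is 0.048 to 0.053 for between-week correlations from 0.9 down to 0. For one outcome it works approximately.

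**4. What it does for three outcomes.** The closed form applies if all tests are independent; the ranges come from simulation, with between-outcome correlation 0 to 0.8 and between-week correlation 0 to 0.9.

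- Each outcome tested on new data at both times: 1 − (1 − 0.0052)³ × (1 − 0.048)³ = 0.151 if independent; range 0.094 to 0.150 (simulated).
- Same histology data judged again at the final level: 1 − (1 − 0.0052)² × (1 − 0.048)³ = 0.146 if independent, since for histology only the looser level then matters.
- Histology judged only at the first look: 1 − (1 − 0.0052)³ × (1 − 0.048)² = 0.108 if independent; about 0.08 when outcomes and weeks are highly correlated.

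Together: about 8% to 15%. The inflation does not hinge on the fraction of 0.5. Any boundary that holds each of three independent outcomes at 0.05 gives 1 − 0.95³ = 0.143.

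**5. Cost of a proper correction.** The HGMX main effect compares 180 with 180, or 180 × 0.85 = 153 per arm after drop-out. Power at the strictest Holm level, 0.05 / 3 = 0.0167:

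- null standard error √(2 × 0.75 × 0.25 / 153) = 0.0495
- alternative standard error √((0.85 × 0.15 + 0.65 × 0.35) / 153) = 0.0482
- z = (0.20 − 2.393 × 0.0495) / 0.0482 = 1.69, so power is 95.5% (98.4% at 0.05).

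**The case against.** The best defence is that section 2.9 already makes the total effective rate the main objective, so the other two outcomes are primary in name only, and O'Brien-Fleming was meant for the two analysis times. The first half softens the point. It does not settle it, because section 2.5.1 gives all three equal standing, section 2.10 does not restrict the confirmatory test, and the Discussion gives healing quality its own week-12 focus. The second half leaves the three outcomes uncorrected.

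Several stronger readings are tempting, but the documents do not support them.

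- *That the week-52 adjustment is needless because those data are complete.* No primary visit is named. One outcome tested at 0.05 at both weeks has type I error of 0.070 (correlation 0.9) to 0.098 (correlation 0), so some adjustment is needed. It is misplaced, not needless. Completeness at the mid-term analysis is also the natural reading, not a stated fact.
- *That eleven outcome-by-visit tests (4 + 2 + 5) give 1 − 0.95¹¹ = 43%.* This tests everything at 0.05 and ignores the boundary that the plan applies. Nine of the eleven are available by week 52, and at 0.0052 each they add at most 9 × 0.0052 = 4.7%. With the boundary applied, all eleven give 9.4% to 13.2%.
- *That the boundary halves the trial's power.* A fall from 81.9% to 52.2% applies to two single groups of 76. The planned pooled comparison keeps about 90% at 0.0052, and that level itself rests on an unstated fraction.
- *That DMC looks break the scheme.* Section 2.11 says "The DMC will have right to decide an interim data analysis and to stop the trial if obvious benefits or harms are observed", but rules for such looks can sit in a charter that is not shown.

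**Conclusion.** The point holds as a misnamed and ineffective multiplicity rule. With two-look levels applied, the family-wise error over the three primary outcomes is roughly 1.5 to 3 times the nominal 5%. The exact value rests on assumptions that the article does not supply: two equally spaced looks, two-sided testing, the correlations between outcomes and weeks, and whether histology is retested at the end. None of the settings examined brings it down to 5%. The poor fit to weeks 52 and 104 is a supporting reason to rewrite the sentence. It does not show that power is lost for nothing, and the planned main-effect comparison is not underpowered.

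**What to change.** Replace the O'Brien-Fleming sentence in section 2.10 with an explicit rule.

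1. First confirmatory test: total effective rate, pooled HGMX versus placebo, at one pre-specified visit, two-sided 0.05.
2. Histological quality and SQD score, each at one named visit, tested next in fixed sequence. Alternatively, apply Holm across the three outcomes.
3. All other visits are secondary. If claims are wanted at both week 52 and week 104, put them in the sequence or split alpha between them.
4. Keep an O'Brien-Fleming-type boundary only for genuine interim looks at the same endpoint on accumulating data.

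**Cost.** No more patients are needed. Two of the three primary outcomes can be claimed only through the hierarchy or at a stricter level, and their power is not documented. The sponsor must choose the primary visit; the article points in more than one direction, and this review does not choose for it. Because the trial is registered and recruiting, the change should be made as a dated amendment, with the registry entry updated, before any unblinded comparison.

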## Introduction

1

Peptic ulcer disease (PUD) is a common digestive system disease that mostly involves the stomach and duodenum, corresponding to a gastric ulcer (GU) and a duodenal ulcer (DU). PUD may occur at any age, but more than half of patients are diagnosed at an age of 30 to 49 years.^[1]^ The global annual incidence of PUD has been estimated to be 0.10% to 0.19% based on physician diagnosis, with an annual prevalence ranging from 2.6% to 4.1%.^[2]^ PUD is a major problem in China, in which the prevalence was up to 17.2% in 2010.^[3]^ The pathogenesis of PUD is chronic damage to the gastroduodenal mucosa, which is mainly attributed to *Helicobacter pylori* (*H pylori*) infection and the use of nonsteroidal anti-inflammatory drugs (NSAIDs)^[4]^; 72.2% of *H pylori*-positive patients and 25% of patients with long-term NSAID use ultimately develop PUD.^[3,5]^

The typical symptoms of PUD are chronic, rhythmic, and periodic upper abdominal pain, as well as distension, belching, and inappetence.^[6]^ PUD can progress to severe complications, including bleeding, perforation, pyloric stenosis, and even cancerization, which may have life-threatening outcomes.^[7]^ Routine treatment of PUD involves a combination of *H pylori* eradication, acid suppression (eg, proton pump inhibitors [PPIs]), and gastric mucosa protection (eg, bismuth agents).^[4]^ This regimen shows definite efficacy, with an ulcer healing rate >90%.^[8]^ However, there are still some concerns with the routine treatment. Gastrointestinal symptoms generally improve significantly after treatment, but systemic symptoms (such as weakness and fatigue) can persist.^[9]^ Moreover, PUD relapse is not uncommon in patients who fail to eradicate *H pylori* and exhibit poor ulcer healing.^[10]^

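### The HGMX-versus-placebo comparison for which the trial was sized depends on a weak interaction pre-test, and no analysis is named if that test is significant

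*Protocol article*

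**What the plan says.** The Sample size estimation section (2.9) fixes the purpose of the trial: "The main objective of this trial is to assess the effects of HGMX compared with placebo on the total effective rate". It assumes a rate of 0.85 in the two HGMX groups together and 0.65 in the two placebo groups together, which is the HGMX main effect of the two-by-two design. The other inputs are "we adopted a type I error (α) of 0.05", "a type II error (β) of 0.2" and 15% drop-out. The result is 360 patients, 90 per group.

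The Data analysis section (2.10) first explores the interaction between HGMX and rabeprazole and continues: "If there are no significant interaction effects, we will compare the main effects of HGMX and rabeprazole". It states no scale and no separate level for the interaction test, and nothing about what follows if the test is significant. The general significance boundary in that section is .05.

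The Discussion links main and interaction effects to the quality of ulcer healing at week 12. It describes the later assessments, including the total effective rate, as HGMX against placebo, without any condition. Section 2.10 does not limit its rule to week 12 or to one outcome.

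**The concern.** The comparison on which the sample size rests should not depend on a preliminary test in the same data. Here it does, and the preliminary test is much less precise than the comparison it controls. Two things can go wrong. A real interaction may be missed, and the non-significant result then read as permission to pool. Or the test may be significant, by chance or because an interaction exists, and the protocol then names no analysis of its main objective. In the second case the analysis would be chosen after the data are seen.

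**Working it through.** **The plan's own figure.** With 0.85 against 0.65, two-sided α = 0.05 (sidedness is not stated) and 80% power, the simple average-rate formula gives n = (1.96 + 0.84)² × 2 × 0.75 × 0.25 / 0.20² ≈ 74. Then 74 / 0.85 ≈ 88 with drop-out, and 4 × 88 = 352, within 3% of 360. So 360 is matched only when the result is applied to each of four cells. The two-against-two comparison would need about 176 in total. Tested without condition, that comparison has 99.4% power with 180 per side, or 98.4% with 153 per side (180 × 0.85).

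**Inputs for the interaction test.** Per arm, 90 × 0.85 = 76.5, taken as 76. The primary analysis is by intention to treat with imputation, so results for 90 are also shown. The level is assumed to be 0.05, two-sided. The protocol gives no interaction size, so sizes of 0, 10 and 20 points are assumed. Every scenario keeps the planned pooled rates of 85% and 65%.

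**Formula.** On the risk-difference scale, z = [(A − B) − (C − D)] / √(Σ p(1 − p) / n), and power ≈ Φ(z − 1.96). At the planned rates the standard error of the interaction is √(0.71 / 76) = 0.097. That of the HGMX main effect is half of this, 0.048.

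| A/B/C/D (%) | Interaction | Σ p(1−p) | z, n = 76 | Power, n = 76 | Power, n = 90 |
|---|---|---|---|---|---|
| 85/60/85/70 | 10 points | 0.705 | 1.04 | 18.0% | 20% |
| 80/55/90/75 | 10 points | 0.685 | 1.05 | 18.4% | 21% |
| 85/55/85/75 | 20 points | 0.690 | 2.10 | 55.5% | 63% |
| 80/50/90/80 | 20 points | 0.660 | 2.15 | 57.4% | 65% |

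The interaction detectable with 80% power is 2.80 × 0.097 = 0.27 with 76 per arm, or 2.80 × 0.089 = 0.25 with 90. Both exceed the whole planned effect of 0.20.

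**Scale.** On the logit scale the standard error is √(Σ 1 / [n p(1 − p)]). With 76 per arm:
- 85/55/85/75: difference 0.898, standard error 0.574, power 35%.
- 80/50/90/80: difference 0.575, standard error 0.603, power 16%.
- A third 20-point pattern, 90/60/80/70, gives 57% on the logit scale and 55% on the risk-difference scale. The effect of scale therefore depends on the cell rates.

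For 80/50/90/80, the same true rates stop the main analysis in 57% of trials on one scale and 16% on the other.

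**The two-step rule, by simulation on the risk-difference scale.**
- No interaction: the pre-test is significant in about 5% of trials. The chance that the main effect is both tested and significant is about 93% (76 per arm) or 94% (90 per arm).
- 20-point interaction, HGMX effects of 30 and 10 points: the pre-test is significant in about 56 to 58% of trials (76 per arm) or 63 to 65% (90 per arm). The chance that the main effect is both tested and significant falls from about 99% to about 41 to 43% (76 per arm) or 35 to 37% (90 per arm).
- No HGMX effect: type I error of the main-effect test, given a non-significant interaction, is 4.9 to 5.4%.
- If the unstated fallback were two unadjusted stratum tests at 0.05, the overall false-claim rate would be about 8.1 to 8.6%.

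**The case against.** **Points that stand.** The sentence says "if", not "only if", and sections 2.9 and the Discussion state the HGMX comparison without a condition. Stratum comparisons are the usual next step after a significant interaction and could be in a fuller document. Because 360 fits a per-cell calculation, A − B and C − D would each have 82% (76 per arm) or 88% (90 per arm) power for 20 points, so usable comparisons would remain if the effect were that large in both strata. With no interaction the main analysis still runs in about 95% of trials. These points limit the damage, but they do not remove the written rule. Section 2.10 gives no other route to the main effect, and the protocol does not name stratum comparisons as its fallback.

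**Stronger readings the documents do not support.** A reader might infer from the Introduction ("This regimen shows definite efficacy, with an ulcer healing rate >90"%) that the rabeprazole groups will do so well that a significant interaction is likely. That figure is a healing rate for the full routine regimen. All four groups receive standard treatment in weeks 1 to 2, and the total effective rate also counts partial improvement. The figure does not fix the four cell rates and does not imply an interaction.

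A reader might also infer that the pre-test spoils the P value of the main-effect test. The design is balanced and the two contrasts are nearly uncorrelated, so its type I error stays near 5%. Some inflation arises only under an unadjusted fallback such as the one simulated above.

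**Against the remedy.** An unconditional pooled effect can describe neither stratum well if the effects differ. That is a reason to report the stratum effects beside it, not to make the main comparison conditional.

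**Conclusion.** The point holds as a defect in a stated rule. The protocol's main objective depends on a test that detects an interaction as large as the whole planned effect only about 55 to 57% of the time on the risk-difference scale, and one half that size 18% of the time. A non-significant result therefore cannot justify pooling, and a significant one leaves the main objective without a named analysis. The cost is about 5% of trials with no interaction, and over half with a 20-point interaction on the risk-difference scale. These sizes rest on assumed interaction values, a two-sided 0.05 level, 76 evaluable per arm and the plain reading of section 2.10. The documents do not show how likely an interaction is, so the check gives no probability that the planned analysis will actually be lost.

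**What to change.** In section 2.10, replace the conditional sentence with two. First, the primary analysis of the total effective rate is always HGMX (A + C) against placebo (B + D), stratified by rabeprazole. Second, A − B, C − D and the interaction, on a named scale, are always reported with 95% confidence intervals, and no significance test decides whether the primary analysis is run. This brings 2.10 into line with 2.9 and the Discussion, and leaves sample size, visits and treatment unchanged. The cost is one of interpretation: if the stratum effects clearly differ, the pooled effect must be read together with them.
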